##### Alcohol Intake

Daily consumption of wine, beer, and spirits (liquor) will be evaluated and measured in units (glasses). For instance, how many units (glasses) of wine, beer, and spirits are consumed per day?

##### Sleep

Sleep behavior will be evaluated and measured as number of hours of sleep and quality of sleep via the following question: How well do you sleep? Possible answers include “No sleep problems,” “Sleep quality could be improved,” and “important sleep problems.”

#### Assessment Methods

##### First Survey

The questionnaire was sent via the institute’s email system to all eligible staff and students during the 2020 COVID-19 confinement period. A brief introduction section prefaced the questionnaires to explain the survey objectives. The survey was open during a brief, 1-week period to assure a full-confinement snapshot. Automated reminders were sent at least 2 times during this period. Submitted survey responses have been stored on the institute’s “evaluation system software,” from where data can be merged and extracted in an Excel spreadsheet for further analyses. As this data management will be fully automated, no special quality control procedures other than regular plausibility control measures (eg, range checks) are planned.

##### Second Survey

The same questionnaire that was used in the first survey will be sent to all eligible staff and students of BFH-DHP about 1 year later (ie, Spring 2021) during the period of “new normality.” The survey will be open during a 2-week period, and automated reminders will be sent to all participants. Because the process will be completely anonymous, the question “Did you volunteer to participate in the same survey last year?” will be added to the questionnaire. This question will allow to extract a set of participants that filled out both surveys and further perform group comparison analyses of lifestyle habits during confinement and under conditions of “new normality.” Furthermore, the second survey will include additional questions on gross anthropometric characteristics (ie, height and weight), sociodemographic characteristics, living status, gender, age, household size, changes in smoking habits, and quality of life.

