### Ethical Approval and Consent to Participate

Prior to the planning of this protocol, the Dean of the Health Department of BFH was informed about the survey, and he approved this study. This cohort study will be performed following the ethical principles of the Declaration of Helsinki. In the introductory section of the survey, eligible participants (staff and students) were informed that the survey is voluntary and anonymous and that no medical data is requested. Participants could also contact the researchers for any information or further questions. Finally, participants were explicitly asked to provide informed consent for participation electronically, by clicking a button at the start of the electronic survey. The second survey will follow the same procedure outlined above. The evaluation system software we intend to use in this study does not allow for any tracing of the respondents.

The cantonal Ethics Committee of Bern is responsible for this research project. The main task of the ethics committees of Switzerland is to examine and approve applications for research projects in the field of human research. The committees evaluate projects that fall under the following definition from Article 2 of the Federal Act on Research involving Human Beings: “This Act applies to research concerning human diseases and concerning the structure and function of the human body, which involves: persons; deceased persons; embryos and foetuses; biological material; and health-related personal data.” We sought clarification from the Ethics Committee of Bern on whether this research project falls within the scope of the Human Research Act and/or to request a written statement in case the project does not need approval by the committee. We thus verified that this study does not need an approval from the ethics committee (Reference number: Kantonale Ethikkomission Bern, KEK Bern, Req-2020-00909).

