### Eligibility Criteria

All students (N=1300; 88% female and 12% male) enrolled in programs at the Bachelor of Science and Master of Science levels as well as all academic and nonacademic employees of BFH-DHP are eligible and will be invited to participate in this comprehensive, web-based survey. BFH-DHP runs these educational programs in the fields of nursing, nutrition and dietetics, midwifery, and physiotherapy. Individuals that are not employed or enrolled at the university will not be eligible for this study.

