#### Data Collection

This electronic survey will be conducted anonymously using the “evaluation system software” of BFH-DHP (EvaSys, Electric Paper EvaluationssystemeGmbH), which is typically used for quality control of lectures, seminars, and other educational products. The validated iPAQ-SF and bMDSC questionnaires will be transferred within the EvaSys-framework to assess participants’ physical activity and nutritional habits. Additional questions on alcohol consumption and sleep behavior will also be added to the survey.

The first survey will be conducted electronically. After closing of the 1-week survey period by the end of April 2020, the data collected will be merged and automatically extracted into an Excel spreadsheet for further analyses. The first survey will be analyzed as a cross-sectional study, in accordance with the official guidelines to analyze iPAQ-SF and adapted bMDSC. The survey results will be subjected to analyses as described in the Statistical Analyses section.

The second survey in May 2021 will also be analyzed as a cross-sectional study using the same procedures as used for the analysis of the first survey in 2020. In addition, a subgroup analyses of participants who volunteered in both surveys will allow for group comparison (during confinement versus after confinement).

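### The participation question identifies repeat responders in the 2021 file only, so the during-versus-after comparison mixes change over time with turnover and selective repeat response

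*Protocol article*

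**What the plan says.** All points are from the protocol article.

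- **Who gets survey 2.** Second Survey: the questionnaire "will be sent to all eligible staff and students of BFH-DHP about 1 year later". Eligibility Criteria ties eligibility to current membership: "Individuals that are not employed or enrolled at the university will not be eligible for this study". Nobody has to have been there in April 2020.
- **How the surveys are linked.** Second Survey adds one item, "Did you volunteer to participate in the same survey last year", and states its use: "This question will allow to extract a set of participants that filled out both surveys". Ethical Approval and Consent to Participate says the software "does not allow for any tracing of the respondents".
- **What is compared.** Data Collection: "The second survey in May 2021 will also be analyzed as a cross-sectional study". It then adds the confinement contrast: "a subgroup analyses of participants who volunteered in both surveys will allow for group comparison (during confinement versus after confinement".
- **What survey 1 holds.** Study Setting says that no personal or sociodemographic information was taken. Data Management plans subgroup analyses by division, academic level and employee status, so I take these three to be recorded. Age, gender, household size and similar items are added in survey 2 only.
- **How the study is described.** The Objective and the Introduction call it longitudinal. The Discussion counts the one-year prospective design among its strengths.

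**The concern.** A set of people who completed both surveys has to be located in both files. The added question is asked in 2021, so it marks only 2021 records. Nothing in the 2020 file marks the same people, and no identifier joins the files.

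At stake is how the study's main 2020 to 2021 result is read. If people who left after April 2020, or who did not answer again, differed in physical activity, diet or sleep from those who stayed and answered, that difference would appear as a change between confinement and the year after. Survey 1 offers almost nothing to adjust with. The gap lies in the questionnaire content, so no analysis plan can close it after survey 2 has been fielded.

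**Working it through.** The article gives no sample size, power or turnover figure for this contrast, so there is no stated figure to reproduce. The numbers below illustrate the mechanism.

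**Inputs from the article:** 823 survey 1 respondents (Results); 1300 people (Recruitment) or more than 1500 (Discussion); expected response around 30% (Discussion); 5% significance level (Statistical Analyses).

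**Assumed inputs:** leaver share of survey 1, L = 10% to 40%; difference between leavers and stayers, d = 0.1 to 0.5 SD; 250 Yes respondents in 2021. For scale, 30% of 1500 is 450 respondents. With the Yes shares implied under step 4, that gives 148 to 256 Yes answers.

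**1. Spurious difference with no true change.** Let stayers have mean S in both years, and let repeat responders be typical of stayers.
- 2020 mean, all 823: (1 − L)S + L(S + d) = S + L·d
- 2021 mean, Yes respondents: S
- Spurious difference: L·d, from 0.10 × 0.1 = 0.01 SD to 0.40 × 0.5 = 0.20 SD

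Selective repeat response among stayers would add a further term of the same kind.

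**2. Error rate.** SE = √(1/823 + 1/250) = 0.0722 SD. The rate is Φ(L·d/SE − 1.96) + Φ(−L·d/SE − 1.96).

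| L | d (SD) | L·d (SD) | L·d/SE | Error rate at nominal 5% |
|---|---|---|---|---|
| 10% | 0.1 | 0.01 | 0.14 | 5.2% |
| 30% | 0.2 | 0.06 | 0.83 | 13.2% |
| 40% | 0.5 | 0.20 | 2.77 | 79% |

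In the middle row the rate is 9.9% with 135 Yes respondents and 16.6% with 400. A larger second survey does not help, because the bias stays while the SE shrinks.

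The SE treats the files as independent, although Yes respondents are among the 823. With within-person correlation ρ the true variance is 1/823 + 1/250 − 2ρ/823. At an assumed ρ = 0.5 the true SE is 0.0632. A test that still uses 0.0722 then rejects in 9.9% of cases in the middle row, instead of 13.2%. The rates are therefore approximate. The bias in SD units is unaffected.

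**3. If the two full waves are compared instead.** With turnover share p, stayer mean S, leaver mean V and entrant mean E, the 2021 minus 2020 difference is [(1 − p)S + pE] − [(1 − p)S + pV] = p(E − V). It is zero if entrants resemble leavers. If they differ from stayers by d in opposite directions, its size is 2pd, or 0.02 to 0.40 SD over the same ranges.

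**4. What a No contains.** The 2020 response rate r is 823/1500 = 54.9% to 823/1300 = 63.3%. Assume an entrant share e of 10% to 40%, equal response in 2021 and correct recall.
- Share answering No: e + (1 − e)(1 − r), from 43% (e = 10%, r = 63.3%) to 67% (e = 40%, r = 54.9%)
- Entrants among the No answers: e divided by that share, from 20% (0.10/0.506) to 65% (0.40/0.620)

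The question cannot show where in that range the No group lies.

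**The case against.** The strongest objection concerns a tempting reading: that new students and staff who joined after April 2020 contaminate the confinement contrast. The documents do not support it. Data Collection limits that contrast to people who report both surveys. A new entrant answers No and, apart from misreporting, is outside it. The ambiguity of the No group matters only if the full waves are compared, which the article does not name as its confinement contrast. Even then the bias depends on entrants against leavers, and with stable intakes it can be near zero. This objection stands in full.

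It can also be said that the article promises a group comparison, names a test for independent groups and never announces a paired analysis. That is correct. It does not rescue the statement that both-survey participants can be extracted, because the 2020 side of the group comparison is still everyone who answered.

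A third objection is that two cross-sections of the same open institution are a legitimate comparison, and that restricting 2021 to people present in April 2020 removes recent entrants from one wave only. This also stands. It is why that restriction belongs among the sensitivity analyses.

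Finally, a status question cannot create pairs or remove leavers from survey 1. True: it removes only the part of the bias that runs along division and status.

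**Conclusion.** The point holds in a limited form. The both-surveys set can be identified in 2021 only, so turnover and selective repeat response enter the planned comparison from the 2020 side, and within-person change cannot be estimated. That follows from the article's own account of anonymity and needs no assumption.

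The size does rest on assumptions. A spurious difference of 0.01 to 0.20 SD, and an error rate from hardly above 5% to about 79%, span everything from negligible to serious. A reader might infer that the comparison is bound to be badly wrong. The documents give neither turnover nor the difference between leavers and stayers, so they do not support that. The change is worth making because it is cheap and cannot be made after survey 2 has been fielded.

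**What to change.** 1. Add one closed item to survey 2 on the respondent's place at BFH-DHP in April 2020: division, and status as BSc student, MSc student, employee, or not at BFH-DHP. It splits the No group, exposes some mistaken Yes answers, and places people who have since changed status in their 2020 stratum.
2. Analyse the wave comparison as two repeated cross-sections treated as independent. Classify 2021 Yes respondents by April 2020 division and status, and standardise them to the survey 1 distribution of both. State that the overlap between the files cannot be modelled.
3. Show two sensitivity analyses: all 2021 respondents, and all 2021 respondents who were members in April 2020.
4. Replace the sentence on extracting both-survey participants. Say that they can be identified in 2021 only, that leavers cannot be removed from survey 1, and that within-person change cannot be estimated. Align the longitudinal description with this.

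The cost is one more question in a survey that already gains several, some extra analysis, and a weaker claim than a longitudinal one. Differences within a stratum, such as study year within BSc, remain uncorrected. If survey 2 has already been fielded, step 1 and the April 2020 classification are lost. Standardisation by current division and status, and the corrected wording, remain possible.

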## Methods

### Study Setting

This study follows a cohort study design and will be carried out at BFH-DHP in Switzerland. Figure 1 illustrates the flow diagram for the research design used in this study. This project is an interdisciplinary cooperation involving colleagues from the Departments of Nutrition and Dietetics and Physiotherapy of BFH-DHP. The contents of the survey will be developed at an interprofessional level.

This cohort study comprises 2 defined study periods: The first study period was in the end of April 2020, when the Swiss Federal Council declared the COVID-19 pandemic as an “extraordinary situation.” The first study was cross-sectional, consisting of an anonymous web-based survey. For the first survey, a questionnaire was sent to the staff and students of all 4 divisions of the institute during the COVID-19 confinement period. The participants’ responses were anonymous, in accordance with the data privacy policy of Switzerland [10]. Participants were not allowed to provide any personal information or other sociodemographic characteristics and living status. Participants could stop and exit the survey at any stage before completion. Anonymous survey procedures are known to yield higher disclosure rates of sensitive or stigmatizing information than nonanonymous procedures. Moreover, higher disclosure rates have traditionally known to be associated with more accurate results than lower disclosure rates [11].

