#### Statistical Analyses

Parametric and nonparametric statistics will be used to report results from both surveys and to compare survey results with reference values obtained from the general population during pre–COVID-19 conditions. For descriptive analyses, central tendencies will be expressed as means or medians, and variation will be expressed as SD and 95% CI or interquartile ranges (25th and 75th percentiles), respectively. Kruskal-Wallis tests with posthoc Bonferroni corrections will be used to assess differences between independent groups. Results will be presented as frequency tables or as figures with boxplots.

For the explorative correlation analysis, health profession divisions, students’ academic level, and employee status will be recoded as follows: nutrition and dietetics = 1, midwifery = 2, nursing = 3, physiotherapy = 4, BSc = 1, MSc = 2, and employee = 3. The Spearman rank order correlation coefficient will be used to assess associations between the different variables under analysis. Results will be presented in a correlation matrix.

Statistical analyses will be conducted using SPSS software (version 26.0; IBM Corp.). Statistical significance will be set at the 5% level of error.

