## Discussion

This paper outlines the study protocol of the survey conducted among BFH-DHP students and employees to evaluate their physical activity, nutritional habits, and sleep behavior during the 2020 COVID-19 confinement. This protocol has been developed as an interdisciplinary collaboration between faculty members of the Divisions of Nutrition and Dietetics and Physiotherapy.

During the same period, similar initiatives were undertaken by other institutes. For example, a large survey developed by a consortium of many international universities aimed to retrospectively evaluate the changes in lifestyle habits among the general population in context of the COVID-19 pandemic [2,15,16].

One of the strengths of our survey is that it will be short (time needed to complete the survey will be less than 10 minutes), limiting the questions to physical activity, nutritional habits, and sleep behavior within a specific setting of students and employees of BFH-DHP. We believe, this will help the participants place special focus on the current and future multipliers of healthy lifestyle habits and their own personal behavioral changes due to a general lockdown effected as a key countermeasure to combat the spread of the COVID-19 pandemic. Another strength of our survey is its prospective design over a 1-year period. Based on the large sample size comprising eligible staff and students (N>1500) and considering the huge impact of COVID-19–related strict measures on both the staff and students, we expect a reasonable response rate (ie, around 30%).
It may be hypothesized that such a confinement period may negatively affect physical activity levels of individuals, in general, and students and employees of BFH-DHP, in particular. In an effort to support the public in maintaining “healthy” physical activity levels, Swiss television channels resumed broadcasting home exercise programs after almost two decades. During this time, popular press reported an increase in the demand for fresh vegetables and fruit, as well as alcoholic beverages. Our survey will aim to verify and, if applicable, quantify such observations and put them in proper context.

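### The 2021 participation item cannot identify returners in the anonymous 2020 data, so the planned during-versus-after comparison in people who answered both surveys cannot be done as described

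*Protocol article*

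**What the plan says.** On the 2020 survey, Study Setting states that responses were anonymous: "Participants were not allowed to provide any personal information or other sociodemographic characteristics and living status". Ethical Approval and Consent to Participate adds: "The evaluation system software we intend to use in this study does not allow for any tracing of the respondents". It also says that the second survey follows the same procedure.

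On linking the two surveys, the Second Survey section offers a single device. Because the process is anonymous, "the question “Did you volunteer to participate in the same survey last year?” will be added to the questionnaire". The section then claims: "This question will allow to extract a set of participants that filled out both surveys".

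On the analysis, Data Collection treats each survey as a cross-section and adds that "a subgroup analyses of participants who volunteered in both surveys will allow for group comparison", with during and after confinement as the two sides. The Discussion lists as a merit: "Another strength of our survey is its prospective design over a 1-year period". The Abstract labels the study a retrospective and prospective cohort and a longitudinal survey.

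**The concern.** To extract the people who answered twice, their records must be found in both files. The item is asked only in 2021, so it can mark rows only in the 2021 file. Nothing described in the article marks the matching rows among the 2020 responses.

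The both-surveys subgroup is the only direct during-versus-after comparison that the article describes, so the longitudinal aim rests on it. If it were attempted with the 2020 file as it stands, a group chosen for returning would face a group not chosen in that way. Any difference between people who return and people who do not would be mixed with change over time. Some of that selection is built in: under Eligibility Criteria, people no longer enrolled or employed are not eligible, so graduates and departed staff are in the 2020 data but cannot answer in 2021.

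**Working it through.** **Step 1. Which records can be flagged.** This step needs no arithmetic.

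- 2020 file (823 respondents, Results): anonymous, no personal or sociodemographic data, no code or key described. Returners cannot be identified.
- 2021 file: the yes/no item is present. Returners can be identified by self-report, subject to recall after a year.
- Link between the files: none. The software permits no tracing. Merging the files into one spreadsheet (Data Management) stacks rows but creates no key.

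The set of people who answered both surveys therefore exists only in its 2021 half.

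**Step 2. What the 2020 side could be.** Without a key, it can be all 2020 respondents or a stratum defined by variables held in both files. The variables named for subgroup analyses are division, BSc/MSc level and employee status (Data Management). They allow coarse alignment of groups, not linkage of people.

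**Step 3. What such a comparison would estimate.** Let r be the share of 2020 respondents who return, and d the returner minus non-returner difference in 2020, in SD units. Measured from the non-returner mean:

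- returner mean = d
- mean of all 2020 respondents = r × d + (1 − r) × 0 = r × d
- with no true change, 2021 returners minus all 2020 respondents = d − r × d = (1 − r) × d

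The same formula applies within a stratum, with that stratum's r and d.

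**Step 4. Illustration.** The article states no sample size calculation, SD, return rate or difference, so there is no figure of its own to reproduce. Only 823 and the 5% level come from the document. The values of r and d are assumptions, and a two-sided test is assumed. With n = r × 823 returners, SE = √(1/n + 1/823) in SD units, treating the two samples as independent. For r = 0.5 and d = 0.2:

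- n = 412
- apparent change = 0.5 × 0.2 = 0.10 SD
- SE = √(1/412 + 1/823) = 0.060
- chance of a significant result with no true change = about 38%

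Each cell below gives the apparent change in SD and, in brackets, the chance of a false significant result.

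| Return share | d = 0.1 | d = 0.2 | d = 0.3 | d = 0.5 |
|---|---|---|---|---|
| 30% (n = 247) | 0.07 (16%) | 0.14 (49%) | 0.21 (83%) | 0.35 (99.8%) |
| 50% (n = 412) | 0.05 (13%) | 0.10 (38%) | 0.15 (70%) | 0.25 (98.5%) |
| 70% (n = 576) | 0.03 (9%) | 0.06 (20%) | 0.09 (38%) | 0.15 (79%) |

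A rank-test simulation (3000 runs, within-person correlation 0.5 assumed) gave 34% at r = 0.5, d = 0.2; 72% at r = 0.5, d = 0.3; and 83% at r = 0.3, d = 0.3. With d = 0 it gave 1.7%. Overlap of people between the files thus does not by itself produce false positives; the bias comes from a difference between returners and non-returners.

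**The case against.** The strongest reply is that the article promises only a group comparison. It nowhere states a paired or within-person estimate. Each survey is analysed as a cross-section in its own right, and the both-surveys analysis is an added subgroup. Anonymity was a deliberate choice, argued in Study Setting on grounds of disclosure. Much of this stands: the two cross-sectional analyses and the comparison with reference values are untouched. It does not rescue the claim that people who answered both surveys can be extracted, because even a group comparison in that set needs their 2020 answers. A statistical analysis plan could not supply the missing key either.

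A reader might infer more than the documents support:

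- **That the plan sets returners against all 2020 respondents and will report selection as change.** The article does not say what the 2020 side would be, and bias arises only if returners and non-returners differ.
- **That the 2020 respondents are an unselected group.** The survey was voluntary, and 823 answered from an eligible population given as 1300 in one place and more than 1500 in another. Both waves are self-selected.
- **That the wrong test is prescribed for the wave comparison.** Statistical Analyses says that Kruskal-Wallis tests "will be used to assess differences between independent groups", but does not tie them to the contrast between 2020 and 2021. That choice may be left to an analysis plan not shown.

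**Conclusion.** The point holds as a contradiction within the protocol article. The 2021 item cannot deliver the set of people that the Second Survey section says it will, and the comparison that Data Collection builds on that set cannot be carried out as described. This rests on the text alone. Within-person change cannot be estimated, and because the 2020 data were collected without a key, linkage cannot be restored.

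The numerical consequence is conditional. It assumes that the analysts would fall back on all 2020 respondents, or a stratum of them, as the comparator. The apparent change would then be (1 − r) × d, of unknown size and zero if d = 0. Over the assumed range it runs from 0.03 to 0.35 SD. These figures show that modest selection could be mistaken for an effect of confinement; they do not predict that it will be.

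The claim should be corrected before the two waves are compared. The design supports two repeated cross-sections with an unknown overlap.

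**What to change.** 1. In Second Survey, delete the statement that respondents to both surveys can be extracted. In Data Collection, delete the during-versus-after comparison in that set.
2. Define the during-versus-after analysis as a repeated cross-sectional contrast of all 2020 with all 2021 respondents, stratified by, or standardised to one common distribution of, division and BSc/MSc/employee status. The plan already uses these as subgroup variables.
3. Use the participation item only within the 2021 file, comparing self-reported returners with first-time responders, as a check on selection. Note that it depends on recall.
4. State that the overlap between waves is unknown, that selection within strata remains after standardisation, and that no within-person change is estimated.
5. Replace the longitudinal and prospective cohort wording, including the strength claimed in the Discussion, with repeated cross-sectional.

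A further contrast that removes only 2021 newcomers is not advised. Leavers would stay in the 2020 data, so people who stayed would again be compared with everyone.

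The cost is changed wording and one standardised contrast on variables already planned; no new data are needed. The longitudinal claim is given up, but the design never supported it.
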